#### Within session safety procedures

The participant’s blood pressure and heart rate will be taken by the researcher immediately before and after the session. While the participant is comfortably seated, the tDCS and ABM will be administered at the same time, that is, participants will engage in ABM training whilst receiving tDCS. Each session will last 20 min. The ABM training will start 5 min after the start of the brain stimulation. ABM training will take place over 10 min and tDCS will then continue for a further 5 min. Participants will be reminded that they have the option to withdraw immediately and terminate their participation in the study if they experience discomfort during tDCS administration, or if they wish to withdraw for any reason that they may or may not wish to disclose.

#### Approach bias modification training

The ABM programme will use an implicit learning paradigm, based on a modified version of the F-AAT.^85 113–115^ In this task, participants are shown computer images of food and control (ie, neutral office) items. They are required to pull (pictures grow bigger) or push (pictures grow smaller) a joystick in response to the outer frame of the picture (round vs rectangular), irrespective of the picture content. The training version of the Food-AAT utilises an implicit learning paradigm by presenting all food pictures in the ‘push’ (ie, avoid) format. The study procedure for ABM administration is aligned with previous research.^50 116^

#### Transcranial direct current stimulation

tDCS (both real and sham) will be delivered using a NeuroConn DC-STIMULATOR PLUS device at a constant current of 2 mA (with a 10 s fade in/out) using two 25 cm² surface sponge electrodes soaked in a sterile saline solution (0.9% sodium chloride). The anode will be placed over the right dlPFC and the cathode over the left dlPFC. This montage has been used in sham-controlled studies on food craving, BN and BED.^59^ The stimulation site will be calculated to correspond to the F3 location, as based on the International 10–20 system. tDCS can occasionally result in mild discomfort during administration (ie, tingling or itching sensation, a slightly metallic taste, occasional redness at the site of the electrodes). Fatigue, headache, nausea and insomnia have been reported as potential adverse reactions.^117^ Participants who are at-risk for adverse effects^76^ will be excluded from the study at the screening stage.

### Data analysis

Data will be analysed with the Statistical Package of Social Sciences (SPSS) version 26. Feasibility outcome data will be analysed with appropriate summary statistics. To determine quality, completeness and variability of the clinical outcome data, descriptive statistical analyses and graphical methods will be used. Intent-to-treat analyses will be performed. The size of the treatment effect on each outcome measure will be the difference in outcome data between those in the two treatment conditions and control condition at post-assessment and follow-up. Group differences will be estimated using linear mixed effects regression models, controlling for the baseline level of the outcome. The goal here is not to determine significant group differences but to establish a suitably precise effect size for the primary outcome at the post treatment assessment. This estimate will be used to guide the sample size of a future efficacy trial. Correlational analyses may be computed to analyse relationships between outcome variables and influences of potential covariates such as demographic variables (ie, gender, age, BMI and clinical variables), that is, start/stopping of psychotherapy, psychotropic medication and presence of comorbidities. Outcome data already obtained for participants who discontinue or deviate from the intervention protocol will be kept and analysed.

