## Study aims

In line with established recommendations for outcomes of feasibility trials,^72^ which at present are supported by the National Institute for Health Research, the primary aim is to assess the feasibility of using concurrent ABM+real tDCS compared with concurrent ABM+sham tDCS as a potential adjunct to TAU in this patient population, and acquire key information to inform the development of a large-scale RCT.

The specific objectives of the proposed feasibility study are to:

Establish the feasibility of conducting a large-scale RCT of ABM+tDCS in patients with BED by assessing recruitment, attendance and retention rates.Determine the practicality of administering both ABM and tDCS simultaneously.Determine the best instruments for measuring outcomes in a full trial by examining the quality, completeness and variability in the data.Estimate the treatment effect sizes and SD for outcome measures to inform the sample size calculation for a large-scale RCT.Evaluate whether the treatment is operating as it is designed by analysing process measures, such as within-session Visual Analogue Scales (VAS) of key ED symptoms.Determine whether patients with BED evaluate concurrent ABM+tDCS as acceptable and credible.Obtain information about patients’ willingness to undergo random allocation to ABM paired with either real or sham tDCS administration, or the wait-list control condition.

A secondary aim is to investigate the potential efficacy of concurrent delivery of both forms of treatment on BED.

This will involve evaluating if:

Concurrent sessions of ABM+real tDCS are superior to ABM+sham tDCS and to wait-list control in terms of frequency of objective binge eating episodes, food cue reactivity, food craving, food intake, ED psychopathology and mood.Concurrent ABM+tDCS is superior to the two other conditions in having an effect on the targeted neurocognitive mechanism (approach bias for high calorie food) and related neurocognitive parameters (ie, impulsivity, delayed gratification, emotional regulation).Concurrent ABM and sham tDCS is superior to the wait-list control in eliciting therapeutic effects on the aforementioned clinical outcomes and neurocognitive mechanisms, yet demonstrates an efficacy level below that of concurrent ABM and real tDCS.

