### Study design

The Investigating Concurrent Approach Bias Modification Training and Transcranial Direct Current Stimulation in Binge Eating Disorder (ICARUS) trial is an exploratory randomised controlled feasibility trial with three parallel treatment conditions; ABM+real tDCS, ABM+sham tDCS and wait-list control. All participants across the two intervention groups will receive a treatment protocol of six sessions of ABM+real/sham tDCS conducted over 3 weeks. The comparator groups of a wait-list control and ABM+sham tDCS are necessary to evaluate the potential effect of real versus sham tDCS in participants with BED. The wait-list control group will be examined at the same time points to control for the possibility that improvements in the intervention groups are simply due to regression to the mean, spontaneous remission or other non-specific time effects. Any participants who are engaging in treatment for their ED will continue with TAU, and thus this selection of comparators is deemed acceptable. Within treatment session measures will involve VAS evaluating mood, stress and ED symptoms. Assessments will be conducted three times during the study; at baseline, post-treatment (week 3) and at follow-up (week 7).

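### The treatment effect carried into the next trial's sample size is defined against the wait-list control and does not name real versus sham tDCS, the comparison the aims put first.

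*Protocol article*

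**What the plan says.** The Data analysis section defines the size of the treatment effect on each outcome as "the difference in outcome data between those in the two treatment conditions and control condition at post-assessment and follow-up". The model comes next: "Group differences will be estimated using linear mixed effects regression models, controlling for the baseline level of the outcome". The stated goal is not significance testing but "to establish a suitably precise effect size for the primary outcome at the post treatment assessment", and then: "This estimate will be used to guide the sample size of a future efficacy trial".

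The Randomisation section describes the wait-list condition as receiving no intervention and calls it the control condition. The Procedure section uses control group in the same sense and places both ABM arms among the intervention groups. On that usage the two treatment conditions are real and sham, and the control condition is wait-list.

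In Study aims, "the primary aim is to assess the feasibility of using concurrent ABM+real tDCS compared with concurrent ABM+sham tDCS". One objective under that aim is: "Estimate the treatment effect sizes and SD for outcome measures to inform the sample size calculation for a large-scale RCT". The first question under the secondary aim is whether real is superior to sham and to wait-list. The third expects sham to do better than wait-list but less well than real. Study design says that the two comparators are "necessary to evaluate the potential effect of real versus sham tDCS in participants with BED", and gives the wait-list arm the narrower job of controlling for regression to the mean, spontaneous remission and time effects.

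**The concern.** The definition puts sham on the treatment side of the effect. The aims and the design rationale put it on the comparator side. The estimate built on that definition is the one handed to the next trial.

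Real versus wait-list contains whatever tDCS adds, plus whatever ABM, attention and expectancy contribute. Real versus sham isolates the tDCS component. According to the Blinding section, it is also the only contrast between double-blinded arms. If a later sham-controlled trial took its effect size from a wait-list contrast, it would be planned on a different quantity from the one it tests. Effect sizes for a later trial are a main product of this study (Sample size and Discussion sections), so the choice of contrast should be settled before results are seen.

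**Working it through.** **The plan's own figure.** The article has no power-based sample size to reproduce. Its only calculation is 60 completers inflated for 10% attrition: 60/(1 − 0.10) = 66.7, against a stated 66 (22 per group). The difference is rounding and does not bear on this point. What is used below is 60/3 = 20 completers per arm.

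**Notation.** Let R, S and W be the baseline-adjusted post-treatment means for real, sham and wait-list, in SD units, scored so that higher is better.

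**Reading A: active arms pooled against wait-list.** The estimate is (R + S)/2 − W, which does not determine R − S. A pooled effect of 0.5 fits each row below. The last column is for a two-sample t-test, two-sided 5%, 80% power.

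| R − W | S − W | R − S | n per arm for R − S |
|---|---|---|---|
| 0.5 | 0.5 | 0 | none suffices |
| 0.6 | 0.4 | 0.2 | 394 |
| 0.7 | 0.3 | 0.4 | 100 |
| 0.8 | 0.2 | 0.6 | 45 |

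The pooled effect equals (S − W) + (R − S)/2. It exceeds R − S only when S − W is more than half of R − S. In the last row it is smaller (0.5 against 0.6), so the error can run either way.

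**Reading B: each active arm against wait-list.** Here R − W = (R − S) + (S − W). The third secondary question expects S − W > 0. If so, R − W exceeds R − S by exactly S − W.

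**Size of the consequence.** The article gives no effect size, SD, alpha or power, so every d here is an assumption. Take R − W = 0.8 and S − W = 0.5, so R − S = 0.8 − 0.5 = 0.3. With a two-sample t-test, two-sided 5%, 80% power:

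- d = 0.8 needs 26 per arm.
- d = 0.3 needs 176 per arm.
- 26 per arm has about 19% power for d = 0.3.
- Over a range for R − S, d = 0.2 needs 394 per arm and d = 0.5 needs 64.

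**Precision in this trial, 20 completers per arm, before any gain from baseline adjustment.**

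- Real versus sham: SE = √(1/20 + 1/20) = 0.316 SD, and the 95% half-width is 1.96 × 0.316 = 0.62 SD.
- Pooled active versus wait-list: SE = √(1/40 + 1/20) = 0.274 SD, and the half-width is 1.96 × 0.274 = 0.54 SD.

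**The case against.** The strongest reply is that one loosely worded sentence is being read as an exclusion. It does not say that the arms are pooled, and it could mean differences among all three conditions. The next sentence speaks of group differences in general. The three-group mixed model can estimate real minus sham directly, and under Reading B it is the difference of two reported contrasts. A reader might infer that the real-versus-sham effect is lost from the trial. The documents do not support that: data and model both allow it, and Study aims lists the comparison among the efficacy questions.

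Two further points stand. The primary aim is worded as feasibility, so real versus sham is not set there as a primary efficacy contrast. The interest in it comes from that aim read with its effect-size objective, from the first secondary question and from the design rationale. Nor is the comparator of the next trial fixed anywhere, so a reader should not infer that it will be underpowered. That would require a sham-controlled design sized on a wait-list contrast.

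The reply that a condensed article leaves model contrasts to an analysis plan goes only part of the way. A full list of contrasts could be left to it. But this article does state a definition of the effect, ties the planning estimate to it, and leaves out the comparison that its aims put first.

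**Conclusion.** The point holds as a defect in the stated planning estimate, not in the design, the data or the model. On the article's own use of terms, the effect carried forward is active against wait-list, while the aims and design rationale point to real versus sham. Under pooling the estimate cannot identify real versus sham. Under separate contrasts, real versus wait-list is larger by the sham-versus-wait-list difference, provided the ordering expected in the aims is true. That ordering is a question under test, so it is not established that a wait-list effect is the larger one.

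The figures of 26 against 176 per arm and about 19% power rest wholly on assumed effects and show direction and possible scale only. They matter for a later trial only if it is sham-controlled. This should be fixed, but it does not threaten the conduct of the present trial.

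**What to change.** In Data analysis, replace the sentence defining the treatment effect with wording such as: The effect size for planning the future trial is the baseline-adjusted difference, ABM+real tDCS minus ABM+sham tDCS, at the post-treatment assessment, reported with its 95% confidence interval and the outcome SD. Real minus wait-list and sham minus wait-list are supporting contrasts, reported separately; the active arms are not pooled.

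All three contrasts come from the mixed model already planned, so no new data, participants or visits are needed. The cost is a planning effect that may be smaller and is less precise: about ±0.62 SD with 20 per arm before baseline adjustment, against ±0.54 SD for a pooled wait-list contrast. An interval that wide makes the stated aim of a suitably precise estimate doubtful for this contrast, so the later sample size should take account of the interval and not only the point estimate.

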### Patient and public involvement

Patients and/or public were not involved in the study design process, however we will obtain 20 intervention participants’ qualitative views on their treatment experience in this study to inform future clinical trials.

## Ethics and dissemination

### Data management and data monitoring

Participant data will be anonymised and all anonymised data will be stored electronically on a password protected computer at the IoPPN. All trial data will be stored in line with the General Data Protection Regulation 2018. Hard copies of participant-related data (ie, General Practitioner letters) will be kept in locked cabinets at the IoPPN, KCL. The final trial data set will not be accessed by anyone other than members of the research team.

Data will be stored on manual files, university and laptop computers. There will be no personal data stored on laptop computers. Confidentiality and anonymity of all personal data will be retained throughout the entire study. Manual files will be securely locked in a lockable filing cabinet, and all electronic files will be password protected. Identifying information will be removed from the data, stored separately and replaced with a numeric identification code. All participants will be allocated a numeric code, which will be used to identify their data. The master list of names which correspond to each participant's numeric identification code will be stored electronically and will be password protected. This information will only be accessible to key researchers involved in the study.

The online component of the assessment will use Online Surveys software (formerly BOS). KCL uses this software for large scale surveys, and it is fully compliant with UK data protection laws. Participants will be emailed the link after the in-person component of each assessment session, and instructed to complete the second online component of the assessment within 36 hours. Participants will also have the option to receive and complete a hard copy version of the questionnaires with a stamped addressed envelope to post back to the study researcher at the IoPPN.

It is intended that the results of this feasibility study will be reported and disseminated at national and international conferences. Research findings may also be disseminated through internal newsletters and publications in collaboration with Beat, the UK’s largest ED charity.

Owing to the size and nature of this small-scale feasibility study, a data monitoring committee was not deemed to be required. There are no scheduled interim analyses and this trial may be prematurely discontinued by the chief investigator on the basis of new safety information.

### Ethics and safety aspects

This trial will be conducted in compliance with the study protocol, the Declaration of Helsinki, the principles of good clinical practice (ICH-E6 guideline), the ICH-E8 guideline and the principles of good clinical practice and in accordance with all applicable regulatory requirements including but not limited to the UK policy framework for health and social care research. All participants will be asked by the study researcher to provide written informed consent prior to enrolment. Participants who are at-risk for adverse side effects^76^ will be excluded from the study at the screening stage (ie, such as those with pregnancy or epilepsy). Current safety parameters of tDCS administration regarding voltage amplitude and duration of brain stimulation sessions will be adhered to. Participants have the option to withdraw immediately and terminate their participation in the study if they experience discomfort during tDCS administration, or if they wish to terminate their participation for any other reason that they may or may not wish to disclose. After each training session, participants will complete the tolerance, discomfort and side effects questionnaire to report any adverse effects of the intervention training session. The researcher will record this description of any reported adverse effects, and record the severity and duration of symptoms and how the adverse effect was managed at the following training session. If a participant reports a new clinical diagnosis or change in medication during their involvement in the study, a decision regarding their continued participation in the study will be made by the research team and withdrawal of the participant may be deemed necessary. Standard KCL insurance and NHS indemnity arrangements apply to this study. To promote study adherence, on completion of the follow-up assessment, each participant will be reimbursed for their time, efforts and travel (£60 for assessments and up to £60 for travel expenses). Additionally, participants in the wait-list control group will be offered the opportunity to receive 6 sessions of ABM+tDCS after the follow-up.

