### Procedure

Figure 1 illustrates the timeline of the study procedures. All participants will partake in assessments at each of the three measurement points; baseline, post-treatment and follow-up. Each assessment will comprise of an in-person study visit with tasks and measures, and online/hardcopy questionnaires and scales to be completed at home by the participant within 36 hours following the study visit. Table 1 details the tasks and measures allocated to each assessment and training visit. After the baseline assessment, participants are randomised to one of three groups: (1) ABM+real tDCS, (2) ABM+sham tDCS or a wait-list control group. Participants allocated to an intervention group will be offered six sessions of ABM+real/sham tDCS across 3 weeks. All study participants may receive TAU, for example, if they are currently engaged in outpatient treatment for their ED. The control group will not receive any study intervention, and any participants receiving outpatient services treatment for their ED will continue TAU during this 3 week period. The post-treatment assessment will be conducted on all participants after the sixth (final) session of ABM+real/sham tDCS for the intervention groups, and 3 weeks after the baseline assessment for the control group. The follow-up assessment will be conducted 28 days after the end of treatment, that is, 7 weeks post-randomisation. A follow-up period is included because if the effects of the intervention result from increased neuroplasticity, behavioural changes may need time to emerge. Assessing the longevity of favourable clinical outcomes beyond the treatment period is also relevant to the objectives of this feasibility study. The researcher conducting the assessment and testing sessions will remain blind to the study condition of intervention group participants until the study data collection period is completed.

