**Figure 1 F1:**
[figure not shown]
Study procedure. The three assessment time points are baseline, post-assessment and follow-up. ABM, approach bias modification training; CG, wait-list control group; IG1, intervention group 1; IG2, intervention group 2; tDCS, transcranial direct current stimulation.

**Table 1 T1:** Study schedule of measurement and testing time points

Approximate time since baseline	Screening of potential participants	Baseline assessment (all participants)	Training: six sessions of ABM+real tDCS 0–3 weeks	Training: six sessions of ABM+sham tDCS 0–3 weeks	Post- assessment (all participants 3 weeks	Follow-up (all participants) 7 weeks
Informed consent		X				
EDDS, SCID-I	X					
tDCS safety screening	X					
Demographic information		X				
EDE-Q^83^		X			X	X
Inhibitory control tasks; Go/No-Go task^105^, SST^107^		X			X	X
Delay discounting task with money and food^103^		X			X	X
Food-related tasks; food choice task^88^, FCT, bogus taste test^102^		X			X	
Approach bias assessment tasks; F-AAT^85^, SRC^87^		X			X	X
Questionnaires and scales (incl. at home); EDRSQ,^119^ FCQ-T-r,^94^ PFS,^95^ YFAS 2.0,^96^ ERQ,^108^ PANAS,^109^ BIS-11,^120^ CIA,^121^ DGI,^104^ DASS-21^110^		X			X	X
Pre-(tDCS+ABM) measures: Multiple VAS, blood pressure, pulse			X	X		
Real or sham tDCS to dLPFC			X	X		
Approach bias modification training			X	X		
Post-(tDCS+ABM) measures: Multiple VAS, blood pressure, pulse			X	X		
Tolerance, discomfort and side effects			X	X		
Acceptability questionnaire						X
Blinding assessment questionnaire						X

ABM, approach bias modification training; BIS-11, Barrett Impulsiveness Scale; CIA, Clinical Impairment Assessment; DASS-21, Depression, Anxiety and Stress Scale; DGI, Delayed Gratification Inventory; dLPFC, dorsolateral prefrontal cortex; EDDS, Eating Disorder Diagnostic Screen; EDE-Q, Eating Disorder Examination; EDRSQ, Eating Disorder Recovery Self Efficacy Questionnaire; ERQ, Emotion Regulation Questionnaire; F-AAT, Food Approach-Avoidance Task; FCQ-T-r, Food Cravings Questionnaire Trait Version–reduced; FCT, Food Challenge Task; PANAS, Positive and Negative Affect Schedule; PFS, the 21-item Power of Food Scale; SCID-I, Structured Clinical Interview for Diagnostic and Statistical Manual (DSM) Axis I Disorders; SRC, Stimulus Response Compatibility Task; SST, Stop Signal Task; tDCS, transcranial direct current stimulation; VAS, Visual Analogue Scale; YFAS 2.0, Yale Food Addiction Scale Version 2.0.

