### Outcome assessment

Measures of feasibility, safety and adherence will be collected throughout the study. Outcomes related to ED symptoms, general psychopathology and neurocognition will be measured before and after the study intervention to assess treatment success. Each assessment session will be split into an in-person visit and at-home component to accommodate time constraints and minimise disruption to task performance due to participant fatigue. The in-person assessment measures will take between 75 - 150 minutes to complete, and the online questionnaires will take approximately 30 minutes.

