### Intervention

In both intervention groups, participants will receive six sessions of concurrent ABM and real or sham tDCS which will be delivered twice a week for 3 weeks. A researcher trained in tDCS administration will deliver the training sessions.

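### Safety is said to be measured for the whole study, but nothing scheduled follows up adverse effects after a participant's last training session

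*Protocol article*

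**What the plan says.** The article sets a broad scope under Outcome assessment: "Measures of feasibility, safety and adherence will be collected throughout the study".

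The collection itself is narrower. Under Ethics and safety aspects: "After each training session, participants will complete the tolerance, discomfort and side effects questionnaire to report any adverse effects of the intervention training session". Any effect reported is then described by the researcher, who also notes its severity, its duration and "how the adverse effect was managed at the following training session".

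In Table 1 the row "Tolerance, discomfort and side effects" is marked in the two training columns (weeks 0 to 3) and nowhere else. It has no mark at post-assessment (week 3) or follow-up (week 7).

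On timing, the Intervention section gives "six sessions of concurrent ABM and real or sham tDCS which will be delivered twice a week for 3 weeks", and the Procedure section says: "The follow-up assessment will be conducted 28 days after the end of treatment, that is, 7 weeks post-randomisation". The section on transcranial direct current stimulation (tDCS) lists the reactions to expect: "Fatigue, headache, nausea and insomnia have been reported as potential adverse reactions".

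**The concern.** The recording rule needs a later training session. For sessions one to five there is one, a few days on. After the sixth, or after the last session attended by someone who stops, there is none, and neither of the two remaining visits carries the side-effects form. An effect noted straight after the last session therefore has no scheduled step for its course, and an effect that starts after that session has no scheduled step at all.

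This matters for three reasons within the article itself.

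- Treatment tolerance is part of the acceptability outcome that is meant to inform the large trial.
- The follow-up visit is justified on the ground that behavioural change may take time to appear. The design thus looks for delayed benefit with a full battery, but has no scheduled instrument for delayed or persisting harm.
- There is no data monitoring committee, and early stopping rests on the chief investigator acting on new safety information. That makes the trial's own capture more important.

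Participants may also leave because of discomfort without giving a reason, so the course of an effect may be least well documented in those who stop.

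**Working it through.** **Inputs.** 22 participants per group (Sample size); two intervention groups with six sessions each (Intervention); follow-up 28 days after treatment ends and 7 weeks after randomisation (Procedure); form completed after each session (Ethics and safety aspects); marks in Table 1.

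The 22 per group comes from the article's total of 66. Its formula gives 60 / (1 − 0.10) = 66.7, against 66 stated, and 66 / 3 = 22. The rounding has no bearing on this point, and 22 is used as stated.

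**Step 1: what is recorded.** Planned sessions, and so planned post-session forms: 2 × 22 × 6 = 264. All 264 carry a form, including every sixth session.

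**Step 2: sessions with no following session.** With full attendance this is one per treated participant: 2 × 22 = 44, and 44 / 264 = 16.7%. The other 264 − 44 = 220 have a later session. If a participant stops after session k (k below 6), the last session attended takes the place of the sixth. The count stays at one for that participant, and the share rises from 1/6 to 1/k of the sessions delivered to that person.

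**Step 3: time without a scheduled form.** Time on study is 7 × 7 = 49 days. The part after treatment is 28 days, or 28 / 49 = 57%. Table 1 schedules no side-effects form in that period or at the visit that ends it.

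**Step 4: the two readings of the clause.** The reference to the next session can attach to the recording (details are written down then) or to the managing (what was done about the effect then). On the first reading the researcher's record of severity, duration and management has no occasion after the last session. On the second, the management part has none, and no time is fixed for learning the duration. Both leave a gap at the same place.

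**Step 5: what is and is not captured in the intervention groups.**

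| Effect | Post-session form | Later step |
|---|---|---|
| Present right after sessions 1 to 5 | Yes | Yes, next session |
| Begins between sessions | No | Can be raised at the next session |
| Present right after the last session | Yes | None scheduled |
| Begins after the last session | No | None scheduled |

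The article gives no time of onset for the reactions it lists. Insomnia, however, concerns the nights after a session and cannot be judged on a form filled in as the session ends. After sessions one to five the next visit can pick it up; after the last session nothing scheduled does.

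**The case against.** The strongest reply is that the form is completed after each session, which includes the sixth and the last one attended by someone who stops. Discomfort scales, blood pressure and pulse are also taken then. A reader might infer that effects of session six go unrecorded, or that 16.7% of sessions have no adverse-effect record. The article does not support that: all 264 planned sessions have a form. This part of the reply stands in full.

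A reader might also infer that the adverse-effect rate will be too low. That is not shown. Counting an effect reported after a session does not depend on following it up, and the article gives no basis for how many effects would begin in the 28 days. The 57% measures calendar time, not missed events.

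A third inference would be that nothing is recorded in the wait-list group and that no comparison rate exists. The form asks about effects of a training session, which that group does not have. The sham group completes the same form on the same schedule under blinding and gives the comparison rate for tDCS. A newly reported diagnosis or altered medication is acted on in any group, withdrawals are recorded with reasons where given, and mood, anxiety and stress scales are given to all three groups at weeks 3 and 7. None of these is a systematic symptom record, but they rule out the claim that all wait-list events are lost.

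Finally, this is a condensed article. The full protocol may hold general adverse-event procedures, and the sentence on scope is introductory. That limits the point but does not remove it. The article prints a complete schedule and a specific recording rule, and these do not match its own statement of scope. The acceptability questionnaire at follow-up and the interviews with 20 participants may bring some late effects to light, but neither is described as a side-effects record.

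**Conclusion.** The point holds in a limited form. The stated scope of safety collection and the printed schedule do not agree. Following the schedule leaves no step for the duration and management of effects present after a participant's last session, or for effects that begin later. The size is one session per treated participant (44 of 264 planned with full attendance) and 28 days with no scheduled side-effects form.

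This rests on 22 per group as stated, on Table 1 as printed, and on no further procedure in the full protocol, which is not shown. If such a procedure exists, the article's passages still need to be reconciled with it.

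Immediate effects and the blinded comparison of real with sham on the post-session form are not in doubt. The finding is a cheap improvement to data collection. It is not evidence of a biased rate, and the absence of a wait-list form is not an error.

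**What to change.** 1. In Table 1, mark the side-effects form at post-assessment and follow-up for both intervention groups.
2. In Ethics and safety aspects, replace the reference to the next training session with *at the next study contact (training session, post-assessment, follow-up or discontinuation)*.
3. Tabulate the results by arm, real against sham, showing effects reported after sessions separately from those first reported at the two later visits.

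Optional: a brief general-symptom record for the wait-list group at the same two visits, if a background rate without any sessions is wanted.

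**Cost.** At most 44 × 2 = 88 additional forms, a few minutes each, at in-person visits that already take place, plus a contact at discontinuation where the participant agrees. A small amendment to the schedule is needed. No new visit is required.
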